## Criteria for the Evaluation of Multiple Myeloma

"Chinese Guidelines for the Diagnosis and Treatment of Multiple Myeloma (Revised in 2017)" and the 2016 International Myeloma Working Group (IMWG)

| **IMWG Response Criteria** | |
| --- | --- |
| **sCR** | The following definition of complete response includes a normal free light chain (FLC) ratio, and a bone marrow biopsy (after calculating ≥100 plasma cells) showing no clonal cells based on immunohistochemical examination (with κ and λ ratios of ≤4:1 or ≥1:2 for the patient). |
| **CR** | Serum and urine immunofixation electrophoresis negative, with no evidence of any soft tissue plasmacytomas, and plasma cells in the bone marrow aspirate <5%. |
| **VGPR** | Immunofixation electrophoresis may detect serum and urine M proteins, but electrophoresis is negative or serum M protein is reduced by ≥90% with urine M protein levels. |
| **PR** | - Serum M protein decreased by ≥50% and 24-hour urine M protein decreased by ≥90% or reached <200 mg/24 h. - If serum and urine M protein cannot be measured, a difference of ≥50% in free light chain (FLC) levels between the affected and unaffected areas can be used as a substitute for the M protein criteria. - If serum and urine M protein testing and serum free light chain testing cannot be performed, plasma cells must be reduced by ≥50% to substitute for the M protein criteria, provided that the baseline percentage of plasma cells in the bone marrow is ≥30%. In addition to these criteria, if present at baseline, the size of soft tissue plasmacytomas (the sum of the products of the maximum vertical diameters of multiple measurable lesions [SPD]) must decrease by ≥50%. |
| **MR** | Serum M protein decreased by ≥25% but ≤49%, and 24-hour urine M protein decreased by 50%-89%. In addition to the criteria listed above, if present at baseline, the size of soft tissue plasmacytomas (SPD) must decrease by ≥50%. |
| **SD** | It is not recommended to use this as a response indicator; the best description of disease stability should be "time to progression estimate." This does not meet the criteria for CR, VGPR, PR, MR, or PD. |

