| **PD** | Meets any one or more of the following criteria:  Any one or more of the following criteria indicate a minimum confirmation of response value increase of 25%.   - Serum M protein (the absolute increase must be > 0.5 g/dL); - If the baseline minimum M component value is ≥5 g/dL, an increase in serum M protein of ≥1 g/dL; - Urine M protein (the absolute increase must be ≥200 mg/24 h); - For patients where serum and urine M protein levels cannot be measured, the difference in free light chain (FLC) levels between the affected and unaffected areas (the absolute increase must be >10 mg/dL); - For patients where serum and urine M protein levels cannot be measured and where the FLC levels in the affected area cannot be measured, the percentage of plasma cells in the bone marrow is not affected by baseline status (the absolute increase must be ≥10%); - New lesions appear, with the SPD of >1 lesion increasing by ≥50% from the lowest value, or the maximum diameter of the original lesion with a minimum diameter >1 cm increasing by ≥50%; if this is the only measurable value of the disease, the number of circulating plasma cells (at least 200 cells per μL) increases by ≥50%. |
| **Clinical relapse** | Clinical relapse requires one or more of the following criteria:   - Direct indicators of disease progression and/or end-organ dysfunction (such as elevated calcium levels, renal failure, anemia, and osteolytic lesions [CRAB symptoms]) associated with potential clonal plasma cell proliferation. This is not used to calculate time to progression or progression-free survival but can be selectively reported or used in clinical practice; - The occurrence of new soft tissue plasmacytomas or bone lesions (osteoporotic fractures do not constitute lesions); - A clear increase in the size of existing plasmacytomas or bone lesions. A clear increase is defined as a ≥50% increase in the SPD of measurable lesions (and ≥1 cm) after consecutive measurements; - Hypercalcemia (>11 mg/dL); - Hemoglobin decrease of ≥2 g/dL unrelated to treatment or other non-myeloma related symptoms; - An increase in serum creatinine of 2 mg/dL or more at the start of autonomous treatment, attributed to myeloma; - Hyperviscosity related to serum paraproteins. |

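### Protocol Appendix 14.4: the FLC substitute for myeloma PR asks for a ≥50% gap between affected and unaffected chains at one visit, not a ≥50% decrease in that gap from baseline

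*Protocol*

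**What the plan says.** All the criteria are in Protocol Appendix 14.4, Criteria for the Evaluation of Multiple Myeloma.

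- **PR, first item (M protein):** "Serum M protein decreased by ≥50% and 24-hour urine M protein decreased by ≥90% or reached <200 mg/24 h".
- **PR, second item (FLC):** it applies under the condition "If serum and urine M protein cannot be measured", and its whole test is that "a difference of ≥50% in free light chain (FLC) levels between the affected and unaffected areas can be used as a substitute".
- **PR, third item (marrow):** where FLC cannot be used either, "plasma cells must be reduced by ≥50% to substitute for the M protein criteria", given a sufficient baseline plasma cell percentage.
- **PR, added condition:** a soft tissue plasmacytoma present at baseline must also shrink by at least 50%.
- **PD:** the row asks for a 25% increase and lists, for subjects without measurable M protein, "the difference in free light chain (FLC) levels between the affected and unaffected areas (the absolute increase must be >10 mg/dL").
- **sCR:** a normal FLC ratio is part of the definition.
- **VGPR:** the row ends with "electrophoresis is negative or serum M protein is reduced by ≥90% with urine M protein levels", and no urine limit follows.

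Section 7.5 and the note under the appendix table count PR in the myeloma ORR. Section 10.6 analyses ORR on the FAS with a 95% confidence interval. Under the Drug Administration Plan in the Synopsis, PR or better after 6 cycles decides whether a subject may continue treatment.

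**The concern.** Response means change from baseline. The FLC item for PR contains none: it asks how far apart the two light chains are at one visit. In myeloma a wide gap between the chains marks disease, and the protocol agrees, because its sCR row requires a normal FLC ratio. As worded, the item can be met by persistent disease and failed by a subject who is close to normal.

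Such subjects can enter the trial. The inclusion criteria in Section 4.4 do not require measurable serum or urine M protein, and kappa and lambda chains with their ratio are scheduled tests (Sections 6.1 and 6.3). The four-week confirmation of a first CR or PR, described in the flowchart notes, would not catch the error, because it would apply the same single-visit rule again.

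The myeloma contribution to ORR is at stake, and so is a treatment continuation decision that rests on PR.

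**Working it through.** The plan states no figure to reproduce. The check compares the rows and then runs a logic test on assumed FLC values.

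**1. Rows side by side**

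| Row | Quantity | Change from baseline or nadir? |
|---|---|---|
| PR, M protein | serum and urine M protein | Yes, a decrease |
| PR, FLC | gap between affected and unaffected chain | None stated |
| PR, marrow | plasma cells | Yes, a reduction |
| PD, FLC | the same gap | Yes, an increase |

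The FLC item for PR is the only one without a direction or a reference point, and no other section restates it.

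**2. When the literal item is met**

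Let A be the affected and U the unaffected chain. The item does not name its denominator.

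- Denominator A: (A − U)/A ≥ 0.5, which gives A/U ≥ 2.0.
- Denominator U: (A − U)/U ≥ 0.5, which gives A/U ≥ 1.5.

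**3. Illustrative subjects**

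The values are assumed, in mg/L, with baseline A = 500, U = 10 throughout and no plasmacytoma. The baseline difference is 490.

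| A at visit | Difference | Change in difference | Literal gap (÷A; ÷U) | Literal item | ≥50% decrease rule |
|---|---|---|---|---|---|
| 500 | 490 | 0% | 98.0%; 4900% | PR | not PR |
| 600 | 590 | +20.4% (100/490) | 98.3%; 5900% | PR | not PR |
| 150 | 140 | −71.4% (350/490) | 93.3%; 1400% | PR | PR |
| 14 | 4 | −99.2% (486/490) | 28.6%; 40% | not PR | PR |

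The subject who rises to 600 is not caught by the PD row. The increase is 20.4%, below 25%, and 100 mg/L is 10 mg/dL, which does not exceed 10 mg/dL.

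The subject who falls to 14 fails the PR item. The MR row has no FLC route and the VGPR row is written in M protein terms. Unless CR or sCR is met, SD is what remains.

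**4. Size per subject**

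Section 4.1 plans 21 to 42 subjects. One misclassified subject moves overall ORR by 1/42 = 2.4 points to 1/21 = 4.8 points.

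**The case against.** The strongest reply is that the intent can be recovered. The table is headed as IMWG criteria, the item is a substitute for M protein criteria that require a decrease, and it sits between two items that do the same. It looks like a translation slip, and an assessor who knows the source may score it as intended. That stands: actual mis-scoring is not shown. It does not make the text right, because assessors score from the protocol.

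Several stronger readings are tempting, and the documents do not support them.

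- **Untreated subjects are scored as responders.** Efficacy is first assessed on D25, after doses on D1, D8, D11 and D15. Baseline values can satisfy the wording, but no untreated subject is scored.
- **A subject whose affected chain doubles still counts as PR.** With U held constant, 500 to 1000 mg/L raises the difference from 490 to 990, which is 102% and 50 mg/dL. With U = 12, 120 to 240 raises it from 108 to 228, which is 111% and 12 mg/dL. Both meet PD.
- **Every subject who normalises is a non-responder.** The CR row has no FLC test and sCR requires a normal ratio, so some of these subjects can still count in ORR.
- **The false PR rate is near 100%, or myeloma ORR is inflated by tens of points.** The protocol gives neither the number of myeloma subjects nor the number without measurable M protein, and Section 10.6 states no myeloma-only ORR. A baseline plasmacytoma also adds a shrinkage requirement.
- **DCR is distorted too.** The myeloma row of Section 7.5 lists ORR only. Under the general DCR definition, a false PR would often have counted as SD anyway.
- **Any urine value passes for VGPR.** The sentence is unfinished, and an unfinished condition is not a permissive one.

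**Conclusion.** The FLC substitute for PR is wrong as written. It omits the decrease from baseline that its neighbouring items and the PD row show was meant, and nothing else in the protocol corrects it.

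The error is limited to myeloma subjects without measurable serum and urine M protein. Within that group, a subject with no baseline plasmacytoma and a persistent gap (ratio of about 2 or more with the affected chain as denominator, 1.5 with the unaffected) meets the literal item with no change, or with a rise short of PD. A subject whose gap nearly closes fails it unless CR or sCR applies.

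The total effect on ORR is unknown because the size of the group is not given. It is about 2.4 to 4.8 points of overall ORR per misclassified subject if the denominator is the planned 42 to 21, and more if the FAS is smaller. The FLC values above only illustrate the logic.

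Efficacy is a secondary purpose, and DLT and MTD decisions do not depend on this item. It is still worth correcting, because it reverses the meaning of response for those it covers and feeds an individual continuation decision. Nothing here takes a view on the continuation rule itself.

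**What to change.** In the PR row of Appendix 14.4, replace the FLC item with: a decrease of ≥50% from baseline in the difference between involved and uninvolved FLC levels. This matches the quantity in the PD row and settles the denominator. In the example above, the unchanged subject (0%) and the subject who rises (+20.4%) are then not PR, and the subjects with falls of 71.4% and 99.2% are.

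Re-score any subject whose response was assessed on FLC, and check whether a PR at 6 cycles rested on it.

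Separately, complete the VGPR urine condition from the source that the appendix cites.

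The cost is two lines in one appendix, carried through a protocol amendment, and re-scoring of the subjects assessed on FLC, whose number the protocol does not give. It needs no new data where the scheduled baseline and follow-up light chain results are on file.

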- RelapsedALL: The reappearance of blasts in peripheral blood or bone marrow (proportion > 5%) after achieving complete remission (CR) following induction therapy, or the presence of extramedullary leukemia.
- Refractory ALL: Defined as meeting any of the following criteria: ① Failure to achieve CR with a standard 4-week induction therapy regimen, and no response after an additional two weeks of chemotherapy. ② Relapse within 6 months of the first remission, classified as early relapse. ③ Relapse more than 6 months after the first remission, but failure of retreatment with the original induction regimen. ④ Multiple relapses (relapse ≥ 2 times).
  1. **Multiple Myeloma（MM）**

According to the "Chinese Guidelines for the Diagnosis and Treatment of Multiple Myeloma (2017 Revision)" and the definition provided by the International Myeloma Working Group (IMWG) in 2016, relapsed or refractory multiple myeloma is defined as follows:

- Relapsed multiple myeloma (MM) refers to patients who have previously achieved at least a minimal response (MR) or better following treatment but then experience disease progression, necessitating the initiation of salvage therapy. It is categorized into clinical relapse and relapse after complete response (CR).

Clinical relapse is defined as meeting at least one of the following criteria: (1)The appearance of new bone lesions or soft tissue plasmacytomas (excluding osteoporotic fractures); (2)A clear increase in existing plasmacytomas or bone lesions (an increase of 50% in the sum of the products of the maximum vertical diameters of measurable lesions, with an absolute value of ≥1 cm); (3)Hypercalcemia; (4) A decrease in hemoglobin of≥20 g/L (unrelated to treatment or non-MM factors); (5)An increase in serum creatinine of≥176.8 µmol/L that is related to MM since the start of MM treatment; (6) Hyperviscosity syndrome related to serum M-protein.

Relapse after complete response (CR) is defined as meeting any of the following criteria: (1)The reappearance of serum or urine M-protein confirmed by immunofixation electrophoresis; (2) A bone marrow plasma cell percentage of ≥5%; (3) Any other signs of progressive disease (PD).

- Refractory Multiple Myeloma (MM) is categorized into primary refractory and relapsed refractory.

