| **Relapse after complete response (used only when the endpoint of the study is disease-free survival)** | Meets any one or more of the following criteria:   - Immunofixation or electrophoresis shows reappearance of serum or urine M protein; - Development of bone marrow plasma cells ≥5%; - Appearance of any other progression markers (such as new plasmacytomas, osteolytic lesions, or hypercalcemia) (as mentioned above). |

*Note: CR = Complete Response, sCR = Strict Complete Response, PR = Partial Response, VGPR = Very Good Partial Response, MR = Minimal Response, SD = Stable Disease, PD = Progressive Disease.*

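### Appendix 14.4 ties a new myeloma lesion to lesion growth, so read literally a new lesion as the sole finding is neither PD nor a PFS event

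*Protocol*

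**What the plan says.** **PD row, Appendix 14.4.** The row opens "Meets any one or more of the following criteria", so one item is enough. Most items are biochemical or marrow-based. The lesion item begins "New lesions appear, with the SPD of >1 lesion increasing by ≥50% from the lowest value" and continues "or the maximum diameter of the original lesion with a minimum diameter >1 cm increasing by ≥50" per cent.

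**Clinical relapse row, same table.** A new lesion is an item of its own here: "The occurrence of new soft tissue plasmacytomas or bone lesions (osteoporotic fractures do not constitute lesions". The first bullet of this row, on end-organ (CRAB) indicators, contains the sentence "This is not used to calculate time to progression or progression-free survival". That sentence stands neither in the row's lead-in nor in the new-lesion bullet.

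**Relapse after complete response row.** Its title limits it to studies whose endpoint is disease-free survival. One of its items is "Appearance of any other progression markers (such as new plasmacytomas, osteolytic lesions, or hypercalcemia", followed by a pointer back to what the table said earlier.

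**Section 4.2, relapsed myeloma at entry.** Any one listed criterion establishes clinical relapse, which the section treats as a form of disease progression. The first is "The appearance of new bone lesions or soft tissue plasmacytomas (excluding osteoporotic fractures".

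**PFS.** Section 10.6 counts the first recorded PD or death. Section 7.5 speaks of objective tumor progression or death.

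**Two neighbouring cells.** The sCR row sets its clonality limit as "with κ and λ ratios of ≤4:1 or ≥1:2 for the patient". The VGPR row ends by mentioning urine M protein without giving a limit.

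**The concern.** The word *with* in the PD lesion item makes the new lesion and the growth of other lesions one joint condition. Nothing else in the row lets a new lesion count alone. The SD row takes whatever meets none of CR, VGPR, PR, MR or PD, so a subject whose only change is a new lesion can land there.

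At stake is the date, and possibly the occurrence, of a PFS event in myeloma subjects. Imaging is one of the few scheduled routes to progression in this group: X-ray is planned, local CT is optional, and marrow examination in the extension depends on clinical need. If a positive image has no unambiguous category, two assessors can classify the same films differently. With 21 to 42 subjects spread over several diseases, a single reclassified event can visibly move a Kaplan-Meier curve.

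**Working it through.** The plan gives no figure for this point, so the check is a comparison of texts plus one line of arithmetic for sCR.

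**Step 1. Classify each pattern by the PD row as printed, then apply Section 10.6.**

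| Finding | PD row | PFS event under 10.6 |
| --- | --- | --- |
| New lesion, SPD of more than one lesion up by ≥50% | PD | Yes |
| New lesion, original lesion's diameter up by ≥50% | PD | Yes |
| New lesion, qualifying rise in M protein, free light chain or marrow plasma cells | PD, by that other item | Yes |
| New lesion only | No item met | No, on a literal reading |

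Only the last line is defective.

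**Step 2. See where a new lesion alone does appear.** It stands by itself under Clinical relapse. If the PFS exclusion covers that whole row, a new lesion alone is outside PFS. If the exclusion covers only the CRAB bullet, the row is silent on PFS for new lesions, but Section 10.6 still counts only PD. Either way the text does not make it a PFS event. The row on relapse after CR also names new lesions, but this trial has no disease-free-survival endpoint.

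**Step 3. Compare with the rest of the protocol.**
- The row on relapse after CR calls new plasmacytomas and osteolytic lesions progression markers and refers back to earlier text. On a literal reading, the earlier PD row does not list them as sufficient.
- Section 4.2 lets the same finding, alone, establish relapse at entry.
- Section 7.5 uses a broader phrase for the PFS event, which could include a new lesion. Section 10.6 uses the narrower PD.

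The same image can thus establish relapse at entry but not clearly count as progression on study.

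**Step 4. Consider the delay.** Imaging in the extension falls every 2 cycles, 2 × 21 = 42 days. The flowchart notes put M-protein testing at the start of each cycle from the second, that is, every 21 days. A biochemical PD item could therefore be met soon after the image, or much later, or not at all. The protocol fixes no minimum delay.

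**Step 5. Check the sCR limits.** Let r be the κ:λ ratio. The printed condition is r ≤ 4 or r ≥ 1/2 = 0.5. Any r below 0.5 passes the first part, any r above 4 passes the second, and any r from 0.5 to 4 passes both. Every r > 0 passes, so these limits exclude nobody. The sCR row still requires a normal free light chain ratio and no clonal cells on biopsy.

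**Step 6. Check the effect on ORR.** For myeloma, ORR = sCR + CR + VGPR + PR + MR. Moving a subject among sCR, CR, VGPR and PR leaves the sum unchanged.

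**The case against.** **The lesion item may be a loosely translated list of alternatives.** The back-reference in the row on relapse after CR, and the phrase about objective tumor progression in Section 7.5, both suggest that new lesions were meant to count. This is plausible, and it is why the point is limited to the literal reading. It does not clear the text: the words as printed join the two conditions, and the other sections point in a different direction.

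**Section 4.2 is an eligibility definition, not a PFS rule.** It uses the same label, Clinical relapse, as the appendix. This stands in part: the mismatch with Section 4.2 is an inconsistency of concept, not a direct contradiction of a PFS rule.

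**PFS is minor here.** DLT and MTD are the primary objectives. PFS is a descriptive Kaplan-Meier summary, and no separate myeloma analysis is specified. This stands and limits the weight of the point.

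A reader might infer more than the documents support:
- *That progression by new lesions is never a PFS event.* It is, whenever qualifying growth or a biochemical or marrow item accompanies the new lesion.
- *That the protocol expressly excludes new lesions from PFS.* The exclusion sits in the CRAB bullet, and extending it to the new-lesion bullet is an inference.
- *That the event is delayed by at least 42 days.* M protein is tested more often than that.
- *That such a subject necessarily stays on treatment.* Section 4.6 refers to evidence of progression and to investigator judgement, without tying either to the PD row.
- *That sCR adds no clonality information beyond CR.* Only the ratio limits are empty.

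**Conclusion.** The concern holds in a narrow form. As printed, the PD row gives no item that a new myeloma lesion meets by itself, and Section 10.6 counts only PD or death. A subject with only a new lesion can be scored SD, with the PFS event recorded late unless another PD item is met. The direction is towards longer PFS.

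The size cannot be derived. The protocol gives neither the number of myeloma subjects nor the share whose progression first shows as a new lesion. The conclusion rests on reading *with* as a joint condition. If the item was meant as a list, the event rule is sound in intent but the wording still allows inconsistent scoring. The effect is confined to a secondary, descriptive endpoint, so this is a correction that should be made, not one that threatens the primary objectives.

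The sCR limits and the unfinished VGPR criterion are secondary wording defects. They leave depth of response poorly defined but do not change ORR.

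**What to change.** 1. In the PD row of Appendix 14.4, split the lesion item into three separate alternatives: appearance of a new lesion; an SPD increase of at least 50% from the lowest value in more than one lesion; a diameter increase of at least 50% in an original lesion that meets the stated size condition.
2. State which Clinical relapse bullets the PFS exclusion covers.
3. Reconcile Section 4.2, Section 7.5, Section 10.6 and the PD, Clinical relapse and relapse-after-CR rows, so that one definition of progression drives PFS.
4. In the sCR row, assign each ratio limit to its light-chain type. In the VGPR row, complete the urine M-protein limit.

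The cost is wording only, with no new test, visit or sample. Myeloma PFS may read slightly shorter. Subjects already assessed should be checked against the clarified PD item so that all are scored by the same rule.
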